### 2.3. Interventions

All the participants in our study will receive acupuncture and warm needling. The acupuncture needles will be sterile, disposable, and 40 mm in length and 0.3 mm in diameter or 25 mm in length and 0.3 mm in diameter. The acupuncture needles would be obtained from the same manufacturer (COSMOS INTERNATIONAL SUPPLIES CO., LTD.). We will perform acupuncture on 12 meridians and choose 2 acupoints in each meridian (Fig. 2A).

**Figure 2. F2:**
[figure not shown]
(A) Acupuncture on 2 acupoints of one meridian. (B) Perform EA and measure electric characteristics using semiconductor analyzer Agilent B1500A/Agilent 4156C; subsequently, add the burned moxa on the acupuncture needles as warm needling. EA = electroacupuncture.

We will add the burned moxa to the handle of the acupuncture needles as a method for warm needling (Fig. 2B). The moxa rolls are made with pure moxa and rolled in rice paper. The moxa rolls will be 1.2 cm in diameter, 1.5 cm long, and weigh about 0.9 g each. The moxa rolls would be obtained from the same manufacturer (MAC Co.). It will take about 5 to 10 minutes for the moxa to burn out.

The acupoints would be: Chize (LU5) and Kongzui (LU6), Shousanli (LI10) and Quchi (LI11), Zusanli (ST36) and Shangjuxu (ST37), Sanyinjiao (SP6) and yinlingquan (SP9), Shaohai (HT3) and Shenmen (HT7), Yanglao (SI6) and Xiaohai (SI8), Weizhong (BL40) and Chengshan (BL57), Taixi (KI3) and Fuliu (KI7), Quze (PC3) and Neiguan (PC6), Waiguan (SJ5) and Zhigou (SJ6), Yanglingquan (GB34) and Guangming (GB37), and Ligou (LR5) and Zhongdu (LR6). The schematic picture of acupoints lists in Figure 3. These acupoints are based on the World Health Organization standard acupuncture point locations.^[21]^

**Figure 3. F3:**
[figure not shown]
The schematic picture of acupoints in our study.

### 2.4. Outcome measurement

The primary outcomes are the electric characteristics of each meridian measured using the semiconductor analyzer Agilent B1500A/Agilent 4156C, which has been used for meridian electricity evaluation.^[20]^ This machine integrates multiple measurements, including fundamental current-voltage (IV), capacitance-voltage, pulsed IV measurement, and analysis capabilities. The IV measurement ranges from 0.1 fA to 1 A and 0.5 µV to 200 V. The maximal pulse forcing is 40 V and the minimal sampling interval is 5 ns.^[17]^ We would adjust the output electrical parameters. Further, the voltage and current will be supplied by the semiconductor analyzer Agilent B1500A/Agilent 4156C and the electric characteristics will be measured immediately as baseline data (before warm needling) (Fig. 2B). After the moxa burns out, we will again measure the electric characteristics (after warm needling).

The secondary outcome is VAS, a tool for pain assessment. The VAS is a self-reported pain rating scale recorded between 0 and 10.^[22]^ A lower score means less pain while a higher score means more pain. VAS has been used to rate the common *De Qi* sensations subjectively, including ache, numbness, heaviness, pressure, and twinge.^[23]^ Hence, we assess the *De Qi* sensations before and after warm needling by VAS.

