## 2. Material and methods

### 2.1. Study design

This is a prospective and observational study that will be conducted by the Department of Chinese Medicine at the Kaohsiung Chang Gung Memorial Hospital and the Department of Physics at National Sun Yat-sen University from March 2022 to December 2022. The participants will be recruited from the students and staff at National Sun Yat-sen University. Our study will enroll 30 healthy participants in 1 group and all of them will receive both interventions, acupuncture and warm needling, and electric measurement. All personal data will be preserved in a locked closet and kept confidential until the end of the experiment when the principal investigator will disclose and analyze the results.

The participants will receive acupuncture, following which we will use a semiconductor analyzer to measure the electric characteristics and evaluate the visual analog scale (VAS) score before warm needling. Subsequently, we will place burned moxa on the acupuncture needles as our warm needling method. After the moxa burns out, we will measure the electric characteristics using the same evaluation method. We will analyze 1 meridian at a time and measure 12 meridians sequentially in this study. Therefore, all participants will undergo 12 sessions of measurements. Finally, we will compare individual electric characteristics data, before and after warm needling, on 12 meridians. The measurements will be completed in 1 day and the participants would not have to return for follow-up. The flow chart of the study design is presented in Figure 1.

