### 2.5. Sample size calculation

The effect indicators of our study are the electric characteristic and VAS score of *De Qi* sensation before and after warm needling. Based on the results of the previous experiment, which applied the semiconductor analyzer to 30 healthy individuals, the different electric characteristic of meridians was obtained by different input direction on the meridians.^[19]^ The electric currents in different directions were 0.49 ± 0.11 and 0.38 ± 0.13 in the Lung meridian.^[19]^ Another study showed that the VAS score of *De Qi* sensations in healthy participants were 1.54 ± 1.62 and 1.87 ± 1.88 in the traditional needle group and special needle group, respectively.^[18]^ Thus, we used G*Power 3.0.1.0 software to calculate our sample size, with power = 0.8, alpha = 0.05, effect size convention *R* = 0.53. The required sample size of each group was calculated to be 30 participants.

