### 2.6. Statistical analysis

Paired *t* test and repeated measure two-way ANOVA will be used to analyze the change of electric characteristics and VAS between baseline data and post-warm needling data of each participant. We set the statistical significance at a *P* value of < .05. Our statistical analyses will be conducted using SPSS for Windows, version 22 (Statistics 22, SPSS, IBM Corp., Chicago, IL).

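### Twelve meridian-level primary comparisons share a flat P < .05 with no single primary test, while n = 30 fits only one paired t test

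*Protocol article*

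**What the plan says.** Section 2.4 defines the primary outcome in the plural and meridian by meridian: "The primary outcomes are the electric characteristics of each meridian measured using the semiconductor analyzer Agilent B1500A/Agilent 4156C". Section 2.1 fixes the number of comparisons: "we will compare individual electric characteristics data, before and after warm needling, on 12 meridians".

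Section 2.6 gives two analyses for the same contrast, "Paired *t* test and repeated measure two-way ANOVA will be used to analyze the change of electric characteristics and VAS", and one decision rule: "We set the statistical significance at a *P* value of < .05". It does not say which analysis is primary, what the two ANOVA factors are, or whether one result must be significant before another is read.

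Section 2.5 sizes the study with a single calculation, "with power = 0.8, alpha = 0.05, effect size convention *R* = 0.53", and arrives at 30. VAS is named as the secondary outcome in section 2.4.

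**The concern.** Followed as written, the plan lets any of 12 before/after comparisons reach significance on a primary outcome at the 5% level. The stated 5% is then the error rate of each comparison and not of the primary conclusion. A significant change on one or two meridians could not be told from chance.

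The sample size makes this worse. It delivers 80% power for one test at 0.05. If the 12 meridians are tested with error control, the stated power is lost; if they are tested without it, the error rate is lost. Sections 2.4, 2.5 and 2.6 agree with each other only if one primary test is named.

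**Working it through.** **Inputs from the protocol article:** 12 meridians (2.1); significance at 0.05 (2.6); alpha 0.05, power 0.8, effect size 0.53 and n = 30 (2.5); one group, measured before and after (2.1). **Assumed, because the article does not give them:** the correlation rho of the changes between meridians (range 0 to 0.9), one electric characteristic per meridian, and, for power, the same dz = 0.53 in every meridian.

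**1. Reproduce n = 30.** For a two-sided paired t test the noncentrality is dz × √n = 0.53 × √30 = 2.903 on 29 degrees of freedom, with critical value 2.045. The noncentral t distribution gives power 0.801; at n = 29 it is 0.787. So 30 is the smallest n reaching 80% for one test. Other readings of 0.53 do not give 30: one-sided paired gives 24, two independent groups give 57 per group, and a correlation of 0.53 gives about 26.

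**2. Family-wise error with no true effect, 12 tests at 0.05.** If independent: 1 − 0.95^12 = 0.460. With correlated changes, by simulation of 12 paired t tests at n = 30:

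| rho | chance of at least one P < .05 |
|---|---|
| 0 | 46% |
| 0.3 | about 40% |
| 0.5 | 32 to 33% |
| 0.7 | 24% |
| 0.9 | 14% |

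**3. Power per meridian under error control, dz = 0.53, n = 30.**
- Bonferroni: alpha = 0.05/12 = 0.00417, critical value 3.110, power 0.434. Reaching 80% would need n = 54.
- Holm, applied only after a significant overall test: about 54 to 56% on average per meridian for rho from 0 to 0.7 (simulated).

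**4. Power of one overall test.** Average each participant's change over the 12 meridians. With a common SD per meridian, the SD of the average is that SD multiplied by √(rho + (1 − rho)/12), so the standardised change becomes 0.53 divided by this factor.

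| rho | factor | dz of the average | power, n = 30, alpha 0.05 |
|---|---|---|---|
| 0.3 | 0.599 | 0.885 | 0.997 |
| 0.5 | 0.736 | 0.720 | 0.968 |
| 0.7 | 0.851 | 0.622 | 0.909 |
| 0.9 | 0.953 | 0.556 | 0.837 |

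**The case against.** The strongest defence has three parts.

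*The two-way ANOVA may already be the overall test.* If its factors are time and meridian, its time main effect is one global comparison. That is possible, but section 2.6 gives it neither factors nor priority, nor a gatekeeping role over the t tests. The fix therefore mainly settles the role of an analysis that may already be planned.

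*The article is condensed, and an analysis plan not shown here may adjust.* It may, and a missing multiplicity section would not be a finding. But the article itself fixes a multiple primary family, a flat threshold and a single-test sample size. An analysis plan that adjusts per meridian would break the stated power; one that does not would leave the error rate inflated.

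*The aim is exploratory and no success criterion is stated.* This tempers the consequences. Still, the article declares primary outcomes, a powered sample size and a significance threshold, and the Discussion predicts a higher current after warm needling.

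Three stronger readings are tempting and should not be made:
- A reader might count several characteristics per meridian from "including fundamental current-voltage (IV), capacitance-voltage, pulsed IV measurement, and analysis capabilities". That sentence describes what the instrument can do; it is not an endpoint list. Two or three characteristics would mean 24 or 36 tests, with 71% or 84% under independence (1 − 0.95^24 and 1 − 0.95^36), but the number to be tested is not stated and these are scenarios only.
- A reader might say that a false positive is more likely than not. For 12 tests every figure is below one half, and measurements on one person in one day may well be positively correlated.
- A reader might infer that the sample size rests on Lung-meridian current alone. Section 2.5 also cites VAS data, and 0.53 does not follow directly from the quoted current figures: 0.11/√(0.11² + 0.13²) = 0.65 at zero correlation, and more with positive correlation.

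**Conclusion.** The point stands for the 12-meridian family, which the article states explicitly and which is sufficient alone. The family-wise error is about 14% to 46% over correlations of 0.9 to 0, against a stated 5%, and would be higher if more than one characteristic were tested. The 80% power holds for one test with dz = 0.53; for a single meridian under error control it is about 43% (Bonferroni) or 54 to 56% (Holm). The error rates assume one characteristic and equal correlation between meridians. The power figures also assume dz = 0.53 in every meridian, which the article does not claim. No correlation in the range examined restores the 5% level.

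**What to change.** In section 2.4, name one primary endpoint: the before/after change in current, at the same applied voltage, averaged over the 12 meridians. In section 2.6, name one primary test: the time main effect for that endpoint, two-sided at 0.05, with the ANOVA factors written out. Test the 12 meridians only if it is significant, with Holm adjustment, and do not let separate unadjusted paired t tests serve as another route to significance. Report other electric parameters as secondary or exploratory with 95% confidence intervals, and keep VAS secondary as already stated. In section 2.5, say that the 80% power refers to the single primary test and not to each meridian.

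The cost is a few sentences and no extra participants. The downside is that claims about a single meridian become harder to reach.

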### 2.7. Data monitoring

Acupuncture, EA, and warm needling are general practices in TCM. Minor adverse side effects of acupuncture and EA include minor bruising, bleeding or pain at needle insertion sites,^[24]^ nausea, sweating, and dizziness.^[25]^ Other complications include pneumothorax and septicemia. Most adverse side effects are minor, and serious complications are rare.^[25]^ The most common adverse events related to warm needling are burns, skin rash, and pain.^[7]^ Warm needling therapy has been reported as a safe method in clinical practices.^[4]^ In our study, acupuncture will be performed by qualified doctors and the acupoints we chose are at the 4 limbs. The procedure will be safe with minimal risk of serious adverse events. The device we use for EA will apply voltage from 1 to 60 V and current under 2 mA. The voltage and current are in the therapeutic range, which means that our study is safe. Additionally, we will perform warm needling, which adds moxa on acupuncture needles and introduces heat stimulation through the needles, and thick cardboard will be placed on the skin surface to prevent burning injury. If serious adverse effects of acupuncture occur, such as fainting or general weakness, the doctor will remove the acupuncture needles and stop the intervention immediately, and we will record the reason for dropping out of the study.

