According to the World Health Organization International Standard Terminologies On Traditional Medicine In The Western Pacific Region, warm needling is a practice of acupuncture in which the needle is warmed during needling by placing a burned moxa stick on the handle of the needle after insertion.^[31]^ This therapeutic technique delivers heat at acupoints to stimulate the circulation of Qi and blood. In TCM theory, this procedure achieves the effect of a warm supplement, which means to activate and restore a decreased function to normal.^[31]^ In the present study, EA, through the semiconductor analyzer Agilent B1500A/Agilent 4156C, applied the same voltage before and after warm needling. Recent meridian studies showed that the meridian has electric characteristics and physical properties.^[17]^ Additionally, improving the conductivity of the meridians could cause higher electric current and lower impedance in the meridians, which could enhance de-qi sensations and increase the therapeutic effect.^[32]^ Since there are different acupuncture manipulations in traditional Chinese theory, a previous study revealed that the electric current measured during acupuncture was significantly larger in supplementation manipulation than in draining manipulation in the meridians.^[20]^ Accordingly, we expected the changing electric characteristics to a higher current after warm needling would be comparable with the current measured before warm needling since warm needling is a supplementation method. There will be new physical discoveries of warm needling, acupuncture plus moxibustion, in our study.

Although the therapeutic effects of warm needling have been affirmed clinically, the mechanism of warm needling has not been widely elucidated. Few studies discussed the association between ionic conductivity and change of temperature in the biophysical field. This is an interdisciplinary study that has not been performed before, whereby TCM professionals cooperated with physics professionals, toward exploring warm needling using new methods and interventions. The results of electric characteristics related to warm needling will give a new perspective on this popular and effective TCM treatment. The electrical intervention and electric characteristics of warm needling are expected to have vast applications in medical treatment.

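### Section 2.4 defines the secondary outcome as a pain scale but uses it to measure De Qi, so a higher score after moxa could mean either

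*Protocol article*

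**What the plan says.** Section 2.4 of the protocol article introduces the outcome as a pain measure: "The secondary outcome is VAS, a tool for pain assessment". It describes the instrument, "The VAS is a self-reported pain rating scale recorded between 0 and 10", and fixes its direction: "A lower score means less pain while a higher score means more pain". The same paragraph then notes that a VAS has been used for De Qi, "including ache, numbness, heaviness, pressure, and twinge", and concludes that the study will assess De Qi "sensations before and after warm needling by VAS".

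Section 2.5 names De Qi, not pain, as the content of the VAS indicator and takes its VAS planning values from an earlier De Qi study. Section 2.6 analyses the change in VAS by paired t test and repeated measures two-way ANOVA, and does not say what a rise or a fall would mean.

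The Discussion says that better conductivity would raise the current, "which could enhance de-qi sensations and increase the therapeutic effect". For the primary outcome it states a direction: "we expected the changing electric characteristics to a higher current after warm needling". It states none for the VAS.

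On safety, section 2.7 says: "The most common adverse events related to warm needling are burns, skin rash, and pain".

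**The concern.** One outcome carries two constructs. The only scale direction that section 2.4 gives belongs to pain, where higher is worse. The only direction that the article gives De Qi is that stronger goes with a better effect. A participant who feels more De Qi after moxa would therefore be recorded, on the scale as defined, as having more pain.

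The intervention makes this more than a matter of wording. Moxa adds heat between the two readings, and pain is among the adverse events that the article lists for warm needling. The second reading can contain heat pain, and the first cannot. With one group measured before and after, no comparator can separate heat pain from De Qi. The analysis would give a valid p-value for a change whose meaning is not settled, and a blended score cannot be split afterwards.

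**Working it through.** The point concerns definition and interpretation, so most of the check is a comparison of passages. The arithmetic only shows what is and is not affected.

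**1. Does the sample size depend on this?** Section 2.5 gives power 0.80, alpha 0.05, effect size 0.53 and n = 30. A two-sided paired t test using the noncentral t distribution, with standardised mean change 0.53, gives n = 30 and power 0.801. The stated figure is reproduced. The one-sided version gives n = 24, so the figure matches a two-sided test, although section 2.5 does not state the sidedness. A two-sided test has the same size and alpha whichever sign is favourable. Neither changes with the reading of the VAS.

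**2. The passages side by side.**

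| Place | Construct | Meaning of a higher score |
|---|---|---|
| 2.4, description of the instrument | pain | more pain |
| 2.4, final sentence | De Qi | not stated |
| 2.5 | De Qi | not stated |
| 2.6 | VAS, construct not named | not stated |
| 3, Discussion | De Qi (the VAS is not mentioned) | stronger De Qi linked to greater effect, hedged |

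The only row that gives the scale a direction is the pain row. The rows that say what the score is for name De Qi.

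**3. The same number read both ways.** The VAS planning values in section 2.5 are 1.54 and 1.87, a difference of 1.87 − 1.54 = +0.33 points. Under the definition in 2.4 this is more pain. Under the Discussion's reasoning it is stronger De Qi and a better effect. This shows the ambiguity of sign only. The figures compare two types of needle, so they do not estimate the change with warm needling.

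**4. What heat pain would do.** As a simple illustration (an assumption), let the observed change be C = D + P, where D is the change in De Qi and P the change in reported pain.
- If D = 0 and P > 0, then C = P > 0. Heat pain mimics a De Qi gain.
- If D > 0 and P > 0, then C = D + P > D. Heat pain inflates the gain.
- With D > 0, C can be zero or negative only if P is negative, that is, if pain falls after moxa.

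Added heat pain therefore pushes the score the same way as a De Qi gain. The documents give no value for P, so the amount of inflation cannot be computed.

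**5. Number of ratings.** If the VAS is taken before and after on each meridian, 12 × 2 = 24 readings per participant. Section 2.1 describes 12 measurement sessions but does not say that the VAS is repeated in each, so 24 is an upper figure under that assumption.

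**The case against.** The strongest reply is that De Qi is clearly intended. The pain sentences in 2.4 can be read as a general description of the instrument, followed by its use for De Qi, and section 2.5 confirms that use. A condensed article need not give the item wording, the anchors shown to participants, or whether the sensations are rated singly or together. The Discussion sentence is cited background hedged with a conditional, and sets no hypothesis for the VAS. Heat contamination is plausible but not shown: the electrical measurement follows burn-out, the abstract pairs the VAS with it, and cardboard protects the skin. The list of adverse events is general, not a rate expected in this study.

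Much of this stands. Using a VAS for De Qi is not a fault, and the intent is probably De Qi. But section 2.4 states the pain definition and direction as those of the secondary outcome itself. That is text in conflict with its use, not a detail left to the case report form. If De Qi is meant, the pain definition is wrong where it stands. The conflict between 2.4 and 2.5 does not depend on the Discussion.

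A reader might go further and infer three things that the documents do not support:
- *Heat pain could reverse the De Qi result.* It raises the score, as De Qi does, so it cannot turn a gain into a fall.
- *A De Qi gain and a drop in pain would cancel.* No passage predicts that pain falls after moxa, and the participants are healthy.
- *A third of a point of heat pain would equal the whole De Qi signal.* The 0.33 is a contrast between needle types, and no amount of heat pain is given.

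**Conclusion.** The concern holds as a conflict between how the secondary outcome is defined and how it is used. If the pain-anchored scale is put to participants as written, a higher score after moxa cannot be attributed to De Qi rather than to needle or heat pain, and heat pain could mimic or inflate a De Qi gain. By how much is unknown.

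The conclusion assumes that the definition in 2.4 reflects the item participants will see; if the form already asks for De Qi intensity, only the text needs correcting. It is a moderate point. It affects a secondary outcome and leaves the primary outcome, n = 30 and the type I error unchanged. It should be settled before the first reading.

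**What to change.** In section 2.4:
- Replace the pain definition and its direction with a De Qi intensity item from 0 (no De Qi sensation) to 10 (strongest imaginable De Qi sensation).
- State that an increase means stronger De Qi, and keep the test two-sided, as the reproduced sample size implies.
- Record pain or heat discomfort as a separate 0–10 rating at the same times, reported as tolerability.

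The rewording costs almost nothing. The separate rating adds one short question at each VAS reading, up to 24 per participant in one day under the per-meridian assumption above. If that load is thought too high, the rewording alone removes the contradiction in the text, but pain and heat discomfort would then go unmeasured and their influence on the De Qi rating could not be examined.
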